## Abstract

**Background:**

Hypertensive disorders, including preeclampsia, complicate 10% of all pregnancies, causing maternal and fetal morbidity and mortality. In Bangladesh, 24% of all maternal deaths are directly attributed to hypertensive disorders. Conventional antenatal care practices often delay or miss detecting hypertensive disorders in pregnancy, which may allow some women to become vulnerable to the adverse consequences of the hypertensive disorders. Regular self-monitoring of blood pressure and weight gain may improve maternal and fetal outcomes among pregnant women at risk of developing hypertensive disorders during pregnancy through early diagnosis, prompt referral, and timely clinical management; however, to undertake a randomized controlled trial of an intervention to reduce adverse consequences of hypertensive disorders in pregnancy, its feasibility must first be determined.

**Objective:**

The objectives of this study are to evaluate the accuracy of a wearable blood pressure monitoring device (Health Gauge) in order to test the design and methods of a future definitive randomized controlled trial, and to examine the feasibility, acceptability, and fidelity of an intervention focusing on regular monitoring of weight gain and self-monitoring of blood pressure for pregnant women at risk of developing hypertensive disorders and their associated complications.

**Methods:**

The study is located in Matlab, Bangladesh will be conducted in two phases. First, a wearable blood pressure device (Health Gauge) will be validated in accordance with the European Society of Hypertension International Protocol (revision 2010). Second, a prospective, two-arm, parallel, and nonblinded randomized controlled external pilot trial will be conducted. In the pilot trial, 70 eligible participants will be individually randomized to the intervention arm, in which pregnant women will self-monitor their blood pressure daily using a wearable device (Health Gauge) and be evaluated monthly by trained health workers for weight gain from 20 weeks of gestation until delivery, or the control arm, in which pregnant women will be assessed for weight gain every two months from 20 weeks of gestation until delivery (1:1 intervention to control allocation ratio using a permuted block randomization method with concealment). All women will receive standard antenatal care.

**Results:**

A validation study of the wearable blood pressure device has successfully been conducted among the general adult population in Matlab, Bangladesh. As of September 2019, the pilot trial has completed enrollment of women who are pregnant (N=70; intervention: n=35; control: n=35) and follow-up of the participants is ongoing. Data analysis is expected to be completed by June 2020, and results are expected to be submitted for publication in August 2020.

**Conclusions:**

The findings of this study will help us to design a comprehensive, full-scale randomized controlled trial to test the efficacy of regular self-monitoring of blood pressure and weight gain during pregnancy, a simple and inexpensive intervention to help to achieve optimal maternal and fetal outcomes in pregnant women at risk of developing hypertensive disorders and their associated complications during pregnancy.

**Trial Registration:**

ClinicalTrials.gov NCT03858595; https://clinicaltrials.gov/ct2/show/NCT03858595

**International Registered Report Identifier (IRRID):**

DERR1-10.2196/16676

## Introduction

### Background

Hypertensive disorders complicate 10% of all pregnancies worldwide [1]. They include chronic hypertension (pre-existing or when detected prior to 20 weeks of gestation), white-coat hypertension (an elevated blood pressure at clinic but normal blood pressure at home), masked hypertension (normal blood pressure at clinic but elevated blood pressure at home), gestational hypertension (elevated blood pressure detected after 20 weeks but no other systemic manifestations), and preeclampsia (elevated blood pressure detected after 20 weeks with proteinuria or biochemical or hematological abnormalities) [2]. Hypertensive disorders during pregnancy lead to severe morbidity and long-term cardiovascular disability in pregnant women and their offspring and are responsible for 14% of all maternal deaths [3,4]. Hypertensive disorders during pregnancy also lead to fetal growth restriction, preterm birth, and increased perinatal mortality [3]. Preeclampsia, a particularly devastating form of hypertensive disorder, is responsible for approximately 70,000 maternal deaths and more than 500,000 perinatal deaths globally each year [2].

In Bangladesh, 24% of maternal deaths are attributable to hypertensive causes [5]. Although the maternal mortality ratio in Bangladesh declined by 40% between 2001 and 2010 [6], the maternal mortality ratio stalled thereafter. The ratio in 2016 of 196 maternal deaths per 100,000 live births was identical to the estimate in 2010. Furthermore, the cause-specific mortality ratio due to hypertensive disorders of pregnancy increased from 39 per 100,000 live births in 2010 to 46 per 100,000 live births in 2016 [5]. Additionally, the prevalence of fetal growth restriction in Bangladesh is manifested in 30.5% of births being small for gestational age which is among the highest in the world. The rate of preterm birth which is 14.1% [7] is also high. Reducing maternal mortality, small for gestational age births, and malnutrition in children under five years age in Bangladesh and other low- and middle-income countries are now the major concerns of many governments and international agencies [8]; however, the most tractable pathways for effective interventions to promote healthy pregnancy, gestational weight gain, and fetal growth remain uncertain.

In conventional practice, pregnant women are evaluated for hypertensive disorders or associated complications during routine antenatal care visits. Standard antenatal care practices often delay or miss detecting hypertensive disorders during pregnancy, which may allow the women to become vulnerable to the adverse consequences of hypertensive disorders. Although, over the last two decades in Bangladesh, there has been an increase in the occurrence of at least one antenatal care (78%) visit during pregnancy, only 31% of women attend the recommended 4 antenatal care visits [6]. Furthermore, the quality of health care, which is fundamental to translating use of antenatal care services into improved maternal and fetal health outcomes, is generally poor in Bangladesh [5]. Weight and blood pressure measurements are two essential components of antenatal care services and should be ensured for quality care. Monitoring weight gain is important because both inadequate and excessive weight gain during pregnancy have been associated with an increased risk of developing hypertensive disorders [9,10]. To achieve an optimal pregnancy outcome, the United States Institute of Medicine provided recommendations for gestational weight gain stratified according to prepregnancy body mass index (BMI). The 2009 US Institute of Medicine guidelines on total gestational weight gain suggest that women who are underweight (BMI less than 18.5 kg/m^2^), normal weight (BMI from 18.5 to 24.9 kg/m^2^), overweight (BMI from 25.0 to 29.9 kg/m^2^) or obese (BMI greater than or equal to 30.0 kg/m^2^) should gain from 12.5 to 18 kg, 11.5 to 16 kg, 7 to 11.5 kg, and 5 to 9 kg, respectively. The recommendations for rates of weight gain during the 2nd and 3rd trimester are 0.51 (range 0.44-0.58) kg/week, 0.42 (range 0.35-0.50) kg/week, 0.28 (range 0.23-0.33) kg/week and 0.22 (range 0.17-0.27) kg/week, respectively, for the same BMI stratification [11]. As blood pressure has a property of circadian and other temporal variations, the current blood pressure measurement practices, which are also subject to interclinician and terminal digit bias, result in misdiagnosis [12]. A better method of hypertension diagnosis in women makes use of multiple measurements taken over continuous monitoring of blood pressure. While 24-hour ambulatory blood pressure monitoring could be an option, it can cause discomfort, particularly during pregnancy and is limited to only 24 to 48 hours of continuous monitoring [13]. In contrast, physiological parameter–derived blood pressure measurement is novel, noninvasive, and convenient to regularly monitor blood pressure. Blood pressure is estimated through linear modeling of extracted physiological parameters and machine learning algorithms that use features such as electrocardiogram (ECG) and photoplethysmography (PPG) derived pulse width and pulse transit time. Health Gauge is an affordable, wrist-worn wearable device that uses pulse width and pulse transit time to provide blood pressure measurements and is convenient for obtaining a picture of blood pressure and heart rate variability over time (Figure 1). Other methods, such as uterine artery Doppler ultrasonography and maternal blood concentrations of angiogenic factors and metabolomics, are also available to predict and monitor hypertension in pregnancy [14]; however, these tools are more expensive and less convenient for use in resource-poor settings including Bangladesh.

**Figure 1 figure1:**
[figure not shown]
Health Gauge blood pressure monitoring device.

As the optimal management of hypertensive disorders of pregnancy remains unclear, the International Society for the Study of Hypertension in Pregnancy recommends that “*every hypertensive pregnant woman be offered an opportunity to participate in research, clinical trials, and follow-up studies*” [2]. We believe a simple intervention such as regular self-monitoring of blood pressure and weight gain has the potential to improve gestational weight gain and perinatal outcomes in pregnant women at risk of developing hypertensive disorders and complications through early diagnosis, prompt referral, and timely management. To undertake a randomized controlled trial of an intervention to reduce adverse consequences of hypertensive disorders during pregnancy raises important practical concerns about the implementation of the study. This exploratory study will address the question of whether a randomized controlled trial is an appropriate design and if it is feasible.

### Objectives

The aims of the pilot trial are to test the design and methods of a future definitive randomized controlled trial and to examine the feasibility, acceptability, and fidelity of an intervention focusing on regular monitoring of weight gain (once a month) during pregnancy using a digital weighing scale and regular self-monitoring of blood pressure (twice daily) using a wrist-worn blood pressure measuring device (ie, Health Gauge) in a sample of pregnant women who are at risk of developing hypertensive disorders and its associated complications. We will also evaluate the accuracy of Health Gauge in measuring blood pressure through validation studies. Acceptability and usability of Health Gauge for continuous self-monitoring of blood pressure in pregnancy will be assessed in the pilot trial.

## Methods

### Overview

The study will be conducted in two phases in Matlab, Bangladesh. Matlab is a low-lying riverine area which is situated 55 km southeast of the capital of Bangladesh. Since 1966, the icddr,b has been running an internationally recognized Health and Demographic Surveillance System involving a population of 230,000 in Matlab, Bangladesh [15]. Registration of vital events such as births, deaths, marriages, and migration are updated by community health research workers every two months. Information on reproductive health outcomes, contraceptive use, breastfeeding, and immunization is also collected.

### Phase 1: Validation of Health Gauge

The Health Gauge device and an artificial intelligence and machine learning–based companion smartphone app will be provided by Salu Design Group Inc. Health Gauge is a compact, wrist-based, cuff-less blood pressure monitoring device that uses a combination of 2-contact ECG and PPG as well as a combination of pulse wave analysis algorithms, machine learning, and neural network computing techniques to calculate blood pressure instantly. The blood pressure data can be synchronized with and accessed from a smartphone through the secure-access app.

In internal quality control preliminary tests, Health Gauge provided precise and accurate blood pressure measurements in adults (personal communication, [name], CEO, Salu Design Group Inc); however, further evaluation is required in our setting to determine whether the device functions effectively and records blood pressure measurements accurately. The validation study aims to assess the accuracy of the device in measuring blood pressure, according to the European Society of Hypertension International Protocol (ESH-IP revision 2010) [16].

A total of 33 participants who fulfill the age, sex, baseline blood pressure, and other requirements will be included in the validation study. For age criteria at least 10 men and 10 women who are 25 years or older, and for baseline blood pressure, 10 to 12 participants with systolic blood pressure in each of three ranges (90 mmHg to 129 mmHg, 130 mmHg to 160 mmHg, and 161 mmHg to 180 mmHg) and 10 to 12 participants with diastolic blood pressure in each of three ranges (40 mmHg to 79 mmHg, 80 mmHg to 100 mmHg, and 101 mmHg to 130 mmHg) will be included. Validation in specific groups such as adolescents or pregnant women may also be carried out with necessary modification of these requirements, and all such changes or additions will be clearly described during reporting. All the participants will be recruited from outpatients of Matlab hospital (icddr,b) or as volunteers residing in Matlab near the hospital.

The validation team will consist of three trained medical doctors (two observers and one supervisor). The gold standard reference blood pressure measurement will use two standard mercury sphygmomanometers and a good quality teaching stethoscope. Simultaneous auscultations will be performed by two observers using the teaching stethoscope. These two observers will be blinded to each other’s readings. The supervisor will verify the blood pressure readings of the other two observers to ensure that the difference between the two observations is less than or equal to 4 mmHg for either systolic or diastolic pressure values. If the difference is greater than 4 mmHg for either, the measurement will be repeated. The supervisor will also measure blood pressure using Health Gauge. The blood pressure measurements will be alternated between the mercury sphygmomanometer and Health Gauge device. In total, nine consecutive blood pressure measurements will be performed in each participant using the mercury sphygmomanometer (5 times) and Health Gauge (4 times).

Data will be analyzed and reported according to the ESH-IP revision 2010 requirements to conclude if Health Gauge passes the validation protocol; the differences between the measurements obtained from Health Gauge and the mercury sphygmomanometer will be classified according to whether the values are within 5 mmHg, 10 mmHg, or 15 mmHg. The differences will be classified separately for systolic and diastolic blood pressure. Details of the methods, procedures, and analysis have been described elsewhere [16,17]. Phase 2 will proceed when Health Gauge has been validated.

### Phase 2: Pilot Randomized Controlled Trial

#### Study Design

This study is designed as a prospective, two-arm, parallel, and nonblinded randomized controlled external pilot trial. Eligible participants will be individually randomized in a 1:1 allocation ratio to the intervention arm, in which pregnant women will self-monitor their blood pressure daily using a wearable device (Health Gauge) and be evaluated for weight gain monthly from 20 weeks of gestation until delivery, or the control arm, in which pregnant women will be assessed for weight gain every two months from 20 weeks of gestation until delivery. All women will receive standard antenatal care.

#### Study Population Eligibility Criteria

Inclusion criteria are pregnant women in Matlab, Bangladesh with a high-risk pregnancy who are between 12 and 16 weeks of gestation and are between 15 and 50 years of age. Exclusion criteria are women who have a congenital malformation or anomaly, a chromosomal abnormality (such as Down syndrome), chronic debilitating illness, diagnosed psychosis, no electricity at home, and never used a smartphone. In this study, a high-risk pregnancy is defined to identify women at risk of developing hypertensive disorders of pregnancy or their complications [3], as a pregnant woman who meets any one or more of the following criteria: had preeclampsia or gestational hypertension in a previous pregnancy, has chronic hypertension, has chronic kidney disease, had pregestational diabetes, has systemic lupus erythematosus or antiphospholipid syndrome, pregnancy is her first pregnancy (nulliparity), is aged 40 years or older, interpregnancy interval is less than 2 years or greater than 10 years, has a BMI of 35 kg/m^2^ or more, has polycystic ovary syndrome, has a family history of preeclampsia, pregnancy is a multiple pregnancy, has pre-existing thrombophilia, used of selective serotonin reuptake inhibitors beyond the first trimester, has donated a kidney, underwent in vitro fertilization, and has a family history of coronary heart disease.

#### Sample Size

Since this is an exploratory study, conventional sample size calculation may not be applicable; however, we will aim for 35 participants in each arm based on the recommendation by Whitehead et al [18] on the required sample size for pilot trials and by considering a conservative (small) effect size for the definitive trial designed with 90% power and two-sided 5% significance. Our sample size calculation takes into account a 20% attrition.

#### Randomization and Allocation Concealment

Participants will be assigned to the intervention or the control arm using a permuted block randomization method with concealment to ensure that the allocation is not made before the participant has given their consent and joined the study. A random allocation sequence will be generated using a computerized random allocation system (RALLOC module in Stata statistical software; version 14.1; StataCorp LLC) for permuted block randomization to ensure comparable allocation numbers at a certain equally spaced points in the sequence of patient assignment and randomization for parallel study design will be used. Reasonably large blocks with variable block size will be constructed to reduce predictability. The random allocation sequence will be prepared in advance by an independent researcher from icddr,b who has no involvement with the trial.

The randomization list will be transferred to health workers via the health research supervisor into sequentially numbered nontransparent sealed envelopes each containing the name of the group (intervention or control) on a card inside the envelope to ensure that the study personnel do not know the order of this list and are unable to predict the next assignment/allocation. Only one block will be supplied at a time from the independent researcher, and the next block will be provided just after completion of the previous block. The envelopes will be kept in a locker in a secured place, and the key of the locker will be available with the health research supervisor. The health research supervisor will not use the key to open the lock until the last envelope given to health worker has been used. The independent researcher will keep a duplicate set of sealed envelopes.

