#### Blinding

Neither the participants nor the investigators and assessors of outcomes can be blinded to allocation because of the nature of service delivery that will be provided, and thus, we are obliged to make the randomized controlled trial nonblinded; however, it should be mentioned that the outcomes of the trial are objective in nature, therefore, the risk of bias is minimal. Furthermore, the randomization, as well as statistical analysis, will be carried out by someone unconnected to the enrollment process.

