#### Participant Enrollment and Follow-up

In Matlab, pregnancies are usually diagnosed by 12 weeks of gestation and recorded by Health and Demographic Surveillance System field staff. We will obtain this information from Health and Demographic Surveillance System and conduct baseline interviews to identify eligible participants for this study. Health worker will continue to conduct baseline interviews and enroll participants whenever newly pregnant women are identified, and to obtain information from the Health and Demographic Surveillance System until the desired sample size is met. Each potential participant will be provided with a consent form in the local language (Bengali). Health worker will also explain the study in detail and answer any questions. If a woman agrees to participate in the study, her signature or left thumb impression and that of a witness will be taken. A health worker will also sign the consent form in front of the woman and the witness on behalf of the principal investigator of the study. Then the health worker will conduct a short interview using a semistructured questionnaire and record the woman’s height and weight. If eligibility criteria are satisfied, the health worker will open the sealed envelope (in sequence and in front of the participant and the witness) that assigns the participant to the allocated group (intervention or control). If the woman does not meet the eligibility criteria, she will be informed that she cannot take part in the study.

Once enrolled, the women will be followed from 20 weeks of pregnancy until delivery. Health worker will visit women in the intervention arm weekly and those in the control arm every two months. Furthermore, health workers will maintain mobile communication with all women to keep track of the progress of the pregnancy. Health worker will collect outcome data from the households and health facilities by follow-up visit or by phone.

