#### Training of the Health Workers Delivering the Intervention

Four skilled and experienced health workers who each have at least 12 years of formal education will undergo a fifteen-day intensive training program, which will include lectures, mock interviews, role play, and field practice at the community level. A training manual will be developed to guide the health workers in the field.

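### Supplying envelopes one complete block at a time discloses block size and boundary, which undoes the protection that variable block size was meant to give

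*Protocol article*

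**What the plan says.** All references are to the protocol article.

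- Study Design sets the ratio: "Eligible participants will be individually randomized in a 1:1 allocation ratio to the intervention arm" or to control.
- Randomization and Allocation Concealment states the protection: "Reasonably large blocks with variable block size will be constructed to reduce predictability". Sealed, opaque, numbered envelopes are used so that "study personnel do not know the order of this list and are unable to predict the next assignment/allocation".
- The same section then ties supply to blocks: "Only one block will be supplied at a time from the independent researcher, and the next block will be provided just after completion" of the preceding one. It adds a rule for the locker: "The health research supervisor will not use the key to open the lock until the last envelope given to health worker has been used".
- Blinding says of the arms that "we are obliged to make the randomized controlled trial nonblinded".
- Participant Enrollment and Follow-up has one person explain the study, take consent and check eligibility. After that, "the health worker will open the sealed envelope (in sequence and in front of the participant and the witness") and learns the arm.
- Training of the Health Workers Delivering the Intervention gives the number in the field: "Four skilled and experienced health workers".

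No block size is stated.

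**The concern.** Variable block size prevents prediction only while nobody can tell where a block starts and ends. Here the delivery unit is the block. Anyone who sees a whole delivery can count the envelopes and so has the block size, and the arrival of the next delivery confirms the boundary. Earlier allocations are known because the trial is open. Once one arm of a block is used up, the remaining envelopes are known by subtraction, and the last envelope of every 1:1 block is always known. The supply rule therefore works against the aim stated in the same section.

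Selection bias is at stake. Opening the envelope after consent does not help if its content can be inferred before a woman is approached or her eligibility is judged. Enrolment is open from 12 to 16 weeks of gestation, which leaves some room for timing. The Blinding section's argument that objective outcomes keep bias minimal concerns how outcomes are measured. It does not concern which women enter which arm.

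Data Analysis plans effect estimates with 95% confidence intervals for the clinical outcomes, and Objectives says the pilot is to test the methods of a definitive trial. Those are the two places where a concealment weakness would matter.

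**Working it through.** The protocol gives no predictability figure, so there is nothing to reproduce. The check computes what the supply rule discloses.

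**Inputs.** Ratio 1:1 (Study Design). Total 70, 35 per arm (Sample Size; Results). Supply of one block per batch (Randomization and Allocation Concealment). No blinding (Blinding). Block sizes are not given; 6 to 14 is an assumption chosen to fit the description of the blocks as reasonably large.

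**Step 1: allocations known with certainty when boundaries are known.** Take a block of size 2m with m per arm. An allocation is certain once the other arm is exhausted, so the certain ones are the run of identical allocations that ends the block. The m allocations to one arm are split by the m of the other arm into m + 1 gaps, so the expected number in the last gap is m/(m + 1). Adding the same for the other arm gives 2m/(m + 1) per block, a share of 1/(m + 1). An exact recursion over the remaining envelopes gives the same values.

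| Block size | Certain per block | Share | Of 70 women |
|---|---|---|---|
| 6 | 6/4 = 1.50 | 25.0% | 17.5 |
| 8 | 8/5 = 1.60 | 20.0% | 14.0 |
| 10 | 10/6 = 1.67 | 16.7% | 11.7 |
| 12 | 12/7 = 1.71 | 14.3% | 10.0 |
| 14 | 14/8 = 1.75 | 12.5% | 8.75 |

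**Step 2: the same with boundaries hidden.** The comparison is an observer who knows the set of possible sizes but not where blocks end, and who updates by Bayes' rule after each allocation (3000 simulated sequences of 70, sizes equally likely).

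| Sizes mixed | Certain, boundaries known | Certain, boundaries hidden |
|---|---|---|
| 6, 8, 10 | (1.50 + 1.60 + 1.67)/24 = 19.9% | 1.6% |
| 8, 10, 12 | (1.60 + 1.67 + 1.71)/30 = 16.6% | 1.4% |

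In women, 70 × 0.199 = 13.9 against 70 × 0.016 = 1.1, and 70 × 0.166 = 11.6 against 70 × 0.014 = 1.0. With smaller blocks (4, 6, 8) the shares are 24.6% and 2.2%.

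**Step 3: overall correct guesses.** Guessing the arm with more envelopes left gives an expected m + (4^m / C(2m, m) − 1)/2 correct per block. For a block of 8 this is 4 + (256/70 − 1)/2 = 5.33, or 66.6%. For mixed sizes, known against hidden boundaries gives 66.5% against 66.1% (6, 8, 10) and 65.3% against 64.7% (8, 10, 12). The gap is under one percentage point, so what the supply rule adds is the certain allocations at the end of each block.

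**The case against.** The strongest reply is that the person who enrols women need not see the boundary. There are two supply steps: researcher to locker, and supervisor to health worker. The locker rule can be read as issuing envelopes singly or a few at a time. Four workers may draw on one block, and each then sees only her own openings unless they pool what they know. This stands. The text does not settle how envelopes reach the workers, so only the supervisor's view of the boundary is clear, and the figures above are upper bounds for an observer who sees everything.

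Three stronger readings are tempting and are not supported.

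- A reader might blame the supply rule for a guess rate of 65% to 71% instead of 50%. Nearly all of that excess comes from permuted blocks in an open trial and remains when boundaries are hidden.
- A reader might take the block-of-4 result, 33% or about 23 of 70 women, as the likely size. Blocks of 4 fit poorly with reasonably large ones.
- A reader might conclude that the pilot's main results are compromised. The primary outcomes are recruitment, retention, adherence and acceptability, reported descriptively, and two of these concern use of the intervention or its device. The clinical outcomes get estimates and intervals but no hypothesis tests. That the same workers collect outcomes is a separate matter: in an open trial they know the arm whether or not it was predictable.

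It is also fair that holding few envelopes on site limits tampering, and that enrolment is complete, so a new supply rule cannot help this cohort. Neither point removes the conflict between the supply rule and the stated purpose of variable blocks.

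**Conclusion.** The point holds, at moderate weight. As written, each batch discloses block size and boundary to the supervisor, and to health workers if they hold the batch or share what they know of it. This contradicts the aim that personnel cannot predict the next allocation.

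For an all-seeing observer and assumed blocks of 6 to 14, at most about 12% to 25% of allocations become certain, roughly 9 to 18 of 70 women, against about 1% to 2% with hidden boundaries. What a single worker could know may be much less. The consequence is a possible selection bias in the secondary clinical estimates and a concealment method that should not be reused unchanged. Nothing in the document shows that any worker predicted or steered an allocation.

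**What to change.** **For the definitive trial.** Issue sequentially numbered envelopes in batches whose size is unrelated to block boundaries, so that an empty batch says nothing about balance. This keeps the on-site stock small, which handing over the whole series at once would not. Alternatively, have the independent researcher release each allocation only after consent and eligibility are recorded. The batch option needs only that researcher, who is already in place, and a rewrite of one paragraph. Release of single allocations also needs the researcher to be reachable at each enrolment.

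**For the enrolled 70.** Report that each batch was one block, give the block sizes, and say how envelopes were issued to the four workers: singly, in part batches or whole, and whether blocks were shared. Then repeat the clinical effect estimates without the women allocated after one arm of their block was full, identified from the allocation list. The cost is one sentence or two of reporting and one sensitivity table. Its intervals will be somewhat wider because roughly 9 to 18 of 70 women drop out of it under the assumed sizes. The main estimates from all randomized women stay as planned.
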